#### Theory-driven and evidence-based

Besides the (multi) systemic approach the intervention is guided by several other psychological theories and evidence-based behavior change techniques. Self-efficacy, for one, is believed to be important when it comes to changing behavior [15, 40]. Therefore an important component of the intervention is raising self-efficacy and empowering the patient, through the use of techniques from solution focused (brief) therapy. The focus is on solutions and the possibilities of the patient rather than the problem. The social network is also empowered to help support the patient. Evidence-based behavior change techniques are used to change specific determinants of behavior [41, 42].

#### Tailored

As each patient is unique and the determinants of their behavior are also unique to them, the specific strategies employed to promote adherence differ per participant. In order to assess the problems experienced by the patient a visual communication aid is used, called the self-management web [43, 44]. Areas are prioritized and determinants of behavior are explored using fit circles (derived from Multi Systemic Therapy) [45]. This allows specific treatment strategies to be developed.

In addition to addressing person-specific determinants, the intervention can be tailored to the individual in other ways. The duration of the intervention can be adjusted to the goals and needs of the patient and the environment, with a maximum of 6 months. The frequency, location and duration of the appointments are tailored to the wishes of the patient and the social network. Various informants and collaborators from the social network can be involved, per participant the key players in the environment are likely to differ.

#### Administrative aspects and monitoring

Data is coded with an unique study-code per participant. The key of the code is safeguarded by the investigator and only the principal investigator and the sub-investigator will have access to this key. Data (questionnaires/interviews) will be kept for 15 years; the handling of these data will comply with the ‘Wet Bescherming Persoonsgegevens’ (Dutch Personal Data Protection). All data from the questionnaires are collected and stored in an online database, which allows for tracking any changes.

A steering committee was involved during the development of this study and remains involved during the RCT. An independent data-manager monitors the study once a year.

### Effect evaluation

#### Primary outcome measure

The primary endpoint of this study is medication adherence registered with EM, since this is referred to as the gold standard [31, 32]. A commonly used device to monitor adherence is the Medication Event Monitoring System (MEMS) bottle caps. However, the MEMS-caps have a few disadvantages such as the need to diverge from the regular Dosette box which may be confusing for patients because they have to use multiple boxes for their medications and they cannot check if they took their medication [46]. Therefore, we are using another innovative device for electronic monitoring, called the Silent Card (Adherence Innovations, Nijmegen). This silent card is being validated and negates the shortcomings of the MEMS-caps. The silent card is less invasive and disruptive for the patient since it can be used in combination with the regular Dosette box. The device can be fixed to the Dosette box and every time the immunosuppressive medication is taken, the patient needs to push a button on the card. Patients who prefer other ways of storing their medication can also use the silent card without making any alterations to their medication regimen, they simply keep the card with their medication and press the button to indicate having taken the medication. A chip registers the dates and times the button on the silent card is pressed. Data is extracted from the Silent Card using an tablet containing Near Field Communication (NFC) and Bluetooth to connect the Silent Card to the SilentReminderE app, specially developed for the Silent Card. This data is then transferred to the computer.

Medication adherence is operationalized as being adherent ≥95% as registered by the EM. We apply this stringent cut-off, as others have done, because of the clinical impact of non-adherence for this patient group [3, 30, 47]. The proportion of days adherent over the 35–215 day period (T1-T2) will be calculated. To assess whether the intervention has a sustained effect we collect EM data over the period T2-T3 (180 days). Similarly, to explore changes over time we will assess the 95% adherence rate per month as well as for the total period.

#### Secondary outcome measures patient

##### Medication adherence

In addition to EM, other secondary outcome measures are also used to assess medication adherence. This is in line with the suggestion of Schafer-Keller et al. [31] to combine several measurements to reach maximum validity. We calculate the Composite Adherence Score (CAS) combining the following measures:
Patient self-report about non-adherence (Basel Assessment of Adherence to Immunosuppressive Medications Scale; BAASIS©-interview).Collateral report – important other about patients’ non-adherence using an Adjusted Basel Assessment of Adherence to Immunosuppressive Medications Scale; BAASIS©-interview.Collateral report – professional about patients’ non-adherence based on varying medication blood levels or behavioral indicators such as missed appointments.

The BAASIS takes both taking and timing into account, as well as drug holidays, reduction of medication doses, and persistence over the last 4 weeks. An affirmative answer on missing a dose (taking), taking IM ≥ 2 h before or after prescribed dosing time (timing), reducing the IM dose, or stopping taking medication completely (persistence) leads to being categorized as non-adherent. Patients also rate their own adherence using a visual analogue scale ranging from 0% (never take medication as prescribed) to 100% (always take medication as prescribed). The BAASIS is recommended for the use as a self-report measure among transplant recipients [1, 48]. An adjusted version of the BAASIS is used for the collateral report of the important other regarding the medication adherence of the patient. The important other is presented with the same questions as the patients on the IM adherence of the patient. Additional to the yes/no, the important other is allowed to answer I don’t know.

The collateral report from the professional is based on a yes/no answer as to whether they think a patient is adherent.

Furthermore, medical data derived from the medical records is also used to give an impression of adherence. We calculate intra patient variability (IPV) using whole blood concentrations of tacrolimus in multiple measurements over time within patients. The method previously described by Borra et al. [49] is used to make this calculation. The following transplant outcomes are collected: rejection of the graft (yes/no), graft loss (yes/no) and kidney functioning (eGFR).

##### Self-management

The 12-item Partners in Health Scale (PiH_NL) [50] is used to evaluate patients’ self-management skills. Patients can answer on a 8-point Likert scale. The PiH-NL consists out of two subscales: 1) knowledge and coping; 2)recognition plus management of symptoms, and adherence to treatment. The Cronbach’s alphas of the subscales were .80 and .72 referring to a good and acceptable internal consistency respectively. The correlation between the subscales was .43 [50].

Blood pressure and body weight are being used as clinical endpoints and are obtained from electronic patient files.

##### Self-efficacy

The Dutch adaptation of the General Self-Efficacy Scale (GSE [51]) is used to assess self-efficacy among patients. The GSE consists of 10 items. The validity of the GSE has been shown across different countries and samples [52]. The internal consistency of the GSE is good (Cronbach’s α .86 for total sample across countries, Cronbach’s α .84 for the Dutch version) [53].

##### Quality of life

Quality of life is assessed with the World Health Organization Quality of Life – Brief Version (WHOQoL-BREF [54]). The WHOQoL-BREF comprises 26 items, which form four domains: physical health, psychological health, social relationships, environment and two items representing overall quality of life and general health. Cronbach’s alphas of the domains vary between .66 and .80, with physical health having the highest internal consistency [55].

##### Mental health

The Hospital Anxiety and Depression Scale (HADS) is a 14-item scale assessing anxiety (HADS-A) and depression (HADS-D), both with seven intermingled items. The HADS was originally developed by Zigmond et al. [56], and the Dutch version has been validated among different groups of Dutch patients [57]. The most recent literature review found a mean Cronbach’s alpha of .83 and .82 for the HADS-A and HADS-D respectively [58]. The Positive and Negative Affect Schedule (PANAS [59];) comprises 20-items and is used to operationalize mental health, reflecting both negative (NA) as well as positive affect (PA). NA can be best characterized as ‘a general factor of subjective distress’ [59], PA as ‘one’s level of pleasurable engagement with the environment’ [59]. The psychometric properties of the Dutch translation of the PANAS are good (Cronbach’s alpha: PA .83, NA: .79) [60].

##### Social support

The Medical Outcomes Study Social Support Survey (MOS-SSS [61]; is used to assess perceived social support. It consists out of emotional support, tangible support, positive social interaction, affectionate support and one additional item. The MOS-SSS has excellent internal consistency, with Cronbach’s alphas ranging from .91 [61]. Since our research group translated this subscale into Dutch, it has not yet been validated. The translation was done by using forward translation (translated independently by two healthcare professionals/researchers and discussed subsequently) and blind backward translation by a native English speaker.

A subscale of the Health Education Impact Questionnaire (HEIQ [62]), Social integration and support, is also used to operationalize social support. It consists out of 5 items, which can be answered on a 4-point Likert scale. The internal consistency of the subscale is good (Cronbach’s alpha .86). We used the Dutch translation of the subscale from Been-Dahmen et al. [44].

In addition to the existing social support scales, we use a self-developed item to assess the extent to which specific persons from the social network support the patient (supplementary file 1). Furthermore, we developed one item to assess if the patient receives help from their social network when it comes to handling, thinking about and taking medication, and if so, from whom (supplementary file 1).

#### Secondary outcome measures important other

Since the patient’s social network also is involved in the intervention, the important other is also be asked to complete the following measures:

##### Mental health

To assess the quality of life of the important other we used the Care-Related Quality of Life Instrument (CarerQol) [63]. This questionnaire consists of two parts, the CarerQol-7D and the CarerQol-VAS. The CarerQol-7D consists of seven statements reflecting seven dimensions of caregiver burden. The CarerQol-VAS is a visual analogue scale ranging from 0 to 10 indicating the level of happiness a caregiver experiences. The CarerQol shows good psychometric properties among various settings [64, 65]. The Generalized Anxiety Disorder Scale-7 (GAD-7, [66]) is used to measure anxiety. This measure consists of 7 items that reflect most of the DSM-IV criteria for generalized anxiety disorder. The psychometric properties of the GAD-7 are good among primary care patients [66], the general population [67] and among a Dutch sample which received a web-based version of the GAD-7 [68]. The Patient Health Questionnaire-9 (PHQ-9 [69]) is used to assess depression. This measure consists of 9 items which represent each of the 9 DSM-IV criteria. The PHQ-9 is a validated instrument both in primary care and other medical settings [69, 70] as well as among the general population [71].

##### Social support

Social support experienced by the important other is assessed using the same instrument as the patients, namely the Medical Outcomes Study Social Support Survey (MOS-SSS). The subscale Social integration and support from the Health Education Impact Questionnaire (HEIQ) has been slightly adjusted for the use among the important other. Two out of five of the items refer to support regarding the condition, in this case the kidney transplantation. For the important other we adjusted the item to ask about support for themselves in relation to the kidney transplantation of the patient. For example, the patient item is ‘I have enough friends who help me cope with my condition’, the item for the important other is ‘I have enough friends who help me cope with his/her condition’. The remaining three items are similar to the items used among the patients.

For the important other we also use the self-developed item regarding which person(s) from their network provide the most support (supplementary file 1).

### Statistical analysis

#### Power calculation

To our knowledge there was no (multi) systemic intervention study carried out among kidney transplant recipients at the time this project commenced, making it difficult to conduct a power analysis based on a comparable study. Therefore, the power calculation is based upon a behavioral intervention study among a group of heart, liver and lung transplanted patients [72]. The intervention group showed an adherence proportion of 95.1% and the control group a proportion of 79.1%. As the MARS-intervention is more intensive than the intervention of Dobbels et al. [72] we will perform an interim analysis when half of the participants have been included. We applied a 2-sided alpha of 0.029 and a power of 0.80. Anticipating a drop-out of 10%, this led to a target of 81 participants in both groups, a total of 162.

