### Study population

#### Patients

The study population consists of kidney transplant recipients, aged 12 years and older, with no limitation to time since transplantation. Patients are required to have a subscription of IM and have a functioning graft at the time of inclusion. Graft functioning may be deteriorating, but as long as IM is required and the patient is not expected to be on dialysis within the next 3 months they can be included. In order to avoid convenience sampling multiple ways of assessing eligibility are being used. Kidney transplant recipients are eligible for inclusion when non-adherence is signaled by either themselves (self-report), or by the nephrologist or nurse practitioner (collateral report – professional) or someone in the patient’s social network (collateral report- social network). These three indicators combined form a composite adherence score (CAS). An affirmative answer on one (or more) of these indicators is sufficient to invite the recipient to participate. A CAS is more sensitive than using a single measure of non-adherence [31, 34–36]. Furthermore, non-adherent patients who do not explicitly acknowledge their non-adherence as a problem can be identified using the CAS. Professionals form an impression of adherence through, for example, conversations with the patient, clinic attendance and blood assay monitoring. Potential participants who meet any of the following criteria will be excluded from participation: 1) patients classified as adherent on all three of the indicators forming the CAS, 2) patients on dialysis or who are expected to start dialysis within the next 3 months, 3) patients who do not understand the Dutch language, 4) patients prior to their first transplant, and 5) patients with severe psychopathology or ongoing psychological treatment. In contrast with most other studies, patients with cognitive limitations (incapacitated) are not excluded from participation because their representative(s) and social network can be involved in the intervention and give complementary information regarding problems the patient is facing.

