### Randomization

Patients participating in the study are randomized after a run-in period, using block randomization at the patient level, at an 1:1 allocation ratio into either one of the two groups: control group or experimental group. Prior to the start of the study the randomization list was generated by a statistician (RT) using a macro [37] in SAS Enterprise Guide 7.13 (SAS Institute Inc., Vary, NC, USA) that automates the random assignment to treatment groups. To prevent predictability of the blocked randomization, block sizes were random and hidden to the researchers and therapists. Since age of the patient can be a confounding variable, in particular being above or below the age of 18 years, age was a stratification factor. Envelopes were numbered in the same order as the randomization list and the group allocation was put in the envelopes after which they were sealed, so that these could be taken to the home of the participant and revealed accordingly.

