#### Primary study parameter

The primary outcome, the proportion of participants that is adherent more than 95% of the 180 days (T1-T2) in both randomization groups as measured by EM, will be analyzed with a chi-test with continuity correction. The cut-off score of 95% is in accordance with the criteria of the Basel Assessment of Adherence to Immunosuppressive Medications Scale: BAASIS interview [48].

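### The 80% power rests on a 79.1% care-as-usual success rate borrowed from another transplant population and not justified for patients enrolled as non-adherent, so it is not established for this trial

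*Protocol article*

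**What the plan says.** The Power calculation section of the protocol article explains that "the power calculation is based upon a behavioral intervention study among a group of heart, liver and lung transplanted patients". It reports the source's results as follows: "The intervention group showed an adherence proportion of 95.1% and the control group a proportion of 79.1"%. It continues: "We applied a 2-sided alpha of 0.029 and a power of 0.80", and then "Anticipating a drop-out of 10%, this led to a target of 81 participants in both groups, a total of 162". Allocation is 1:1 (Randomization). The section concedes that no comparable study existed, but only in the sense that no (multi)systemic intervention had been tested in kidney recipients. It makes no adjustment for the type of patient enrolled.

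The primary endpoint is binary for each patient: "the proportion of participants that is adherent more than 95% of the 180 days (T1-T2"), compared by a chi-square test with continuity correction (Primary study parameter). Of the 95% threshold the article says "We apply this stringent cut-off, as others have done" (Primary outcome measure).

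On entry, the Patients section states: "Kidney transplant recipients are eligible for inclusion when non-adherence is signaled by either themselves (self-report"), or by a professional, or by someone in the social network. One positive indicator is enough, and patients rated adherent on all three are excluded. The Background defends this selection on the ground that an intervention effect cannot be shown in people who already adhere.

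**The concern.** A trial that selects for non-adherence and then applies a strict threshold would be expected to see a modest success rate under usual care. The sample size instead presumes that about four in five control patients succeed. That sits badly with the Background's reason for selecting non-adherent patients, and the article does not reconcile the two.

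The control rate fixes the variance, the detectable difference and the power. If it is wrong, the 80% does not describe this trial, and a non-significant result would be read against an assurance the design may not give. The article also calls the imported figures only adherence proportions. It does not say whether they are shares of patients above a threshold, which is what the endpoint needs.

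**Working it through.** **Inputs.** From Power calculation: rates 0.791 and 0.951, two-sided alpha 0.029, power 0.80, drop-out 10%, 81 per arm. From Primary study parameter: continuity-corrected chi-square. The control rates of 30–70% are an assumption, because the article gives no EM-based rate for this population.

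**Step 1: reproduce the plan's figure.** Arcsine formula for two proportions, n = 2(z₁ + z₂)²/h², with h = 2·arcsin√0.951 − 2·arcsin√0.791 = 0.503, z₁ = 2.183 (alpha 0.029) and z₂ = 0.842:

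n = 2 × (3.025)² / (0.503)² ≈ 72.3, so 73 evaluable per arm; 72.3/0.9 = 80.3, so 81 randomised.

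The target is therefore reproduced with 79.1% as the control-arm responder rate. Exact power of the uncorrected chi-square at 73 per arm is 0.80, which agrees.

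**Step 2: the planned test at the plan's own rates.** Summing the binomial probabilities of all outcomes in which the continuity-corrected chi-square is significant at 0.029, with 73 per arm, gives power 0.69, not 0.80. The detectable difference at 80% power is about 17.5 points. This shortfall comes from the test and has nothing to do with the population.

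**Step 3: vary the control rate.** Same test, n and alpha. Column 2 keeps the 16-point gain. Column 3 is the smallest gain with 80% power, searched in 0.5-point steps. Column 4 keeps the implied odds ratio, (0.951/0.049)/(0.791/0.209) = 5.13.

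| Control rate | Power, +16 points | Detectable gain (points) | Power, odds ratio 5.13 |
|---|---|---|---|
| 30% | 0.37 | 26 | 0.99 |
| 40% | 0.32 | 26.5 | 0.99 |
| 50% | 0.35 | 25.5 | 0.98 |
| 60% | 0.39 | 24 | 0.96 |
| 70% | 0.49 | 21 | 0.88 |
| 79.1% (plan) | 0.69 | 17.5 | 0.69 |

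**Step 4: separate the two causes.** For a 16-point gain, the fall from 0.80 to 0.69 is due to the continuity correction at the plan's own rates. The further fall from 0.69 to 0.32–0.49 is due to the control rate.

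Like the plan's own figure, these calculations treat a single comparison at alpha 0.029. They count nothing for the interim look.

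**The case against.** The best counter-argument is that entry and endpoint are different measures. One positive indicator suffices, and the professional's indicator is an impression. On the BAASIS, one missed dose, or one taken two hours or more off time, in four weeks counts as non-adherence. One affected day in 28 still leaves 27/28 = 96.4% of days adherent. An eligible patient can therefore exceed 95% over 180 days. This stands. A reader might infer that the eligibility rule rules out a 79.1% control rate, and the documents do not support that. The rate is unjustified and hard to square with the Background, but not logically excluded.

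A second objection is that low power follows only if the gain stays at exactly 16 points. The article never says the absolute difference carries over, it describes MARS as more intensive than the source intervention, and a lower control rate leaves more room to improve. This also stands, as the odds-ratio column shows.

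Third, borrowing rates from a related study is ordinary, and inclusion has already stopped because of Covid-19 (Procedure), so restating power changes neither the sample nor the analysis. Borrowing is indeed ordinary. Borrowing a control rate at odds with the trial's own selection rationale, without comment, still needs an explanation, because the result will be read against the stated power.

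**Conclusion.** The point holds in a limited form. The arithmetic behind 81 per arm is sound for its inputs, but the control rate is carried over from a different population, without justification, to patients flagged as non-adherent. The stated 80% power is therefore not established for this trial.

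Over assumed control rates of 30–70%, with 73 evaluable per arm, power for a 16-point gain is 0.32–0.49, and 80% power needs a gain of about 21–26.5 points. The right comparators under the planned test are 0.69 and 17.5 points at the plan's own rates, so part of the gap from 0.80 belongs to the continuity correction.

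Two further inferences should be resisted. One is that the trial is underpowered: if the odds ratio of 5.13 carried over, power would be 0.88–0.99, so the direction of the error depends on the effect scale and on an unknown control rate. The other is that 95.1% and 79.1% are mean adherence values. The article does not say what they are, and this cannot be settled from the article alone. The primary test remains valid. What needs changing is the power statement.

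**What to change.** In Power calculation, state what the imported 95.1% and 79.1% measure: a share of patients above a threshold (and which threshold) or something else. Replace the single power statement with a short table of power and detectable difference under the planned continuity-corrected test, over control rates of 30–80%, for the number actually randomised.

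Inform the table with the pooled EM data from the run-in (T0–T1). These precede randomisation, so tabulating them reveals nothing about treatment effect. Two caveats should be stated with them. They cover only about 35 days rather than 180. They also probably overstate the control rate, because by the Procedure section's own account adherence is higher when patients start using the device. They should guide where in the table to look, not supply a single replacement rate.

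The cost is a few lines of text and one tabulation. No extra patients are needed and the analysis does not change. The only downside is that the stated power may become less favourable.

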### Procedure

Inclusion commenced in September 2018, but inclusion is recently stopped due to Covid-19. Data collection is still ongoing. Participants are being recruited from one academic hospital in the Netherlands where they received their kidney transplant or from the local hospital after referral for post-transplant care. Patients who are eligible for the study are informed about the study by the healthcare professional at the end of their regular appointment. Thereafter the healthcare professional or someone from the research team hands out written information on the study (PIF). The healthcare professional was provided with a standardized script on introducing the study. After having time to consider participation, the researcher contacts the patients by telephone to provide additional information (when needed), answer questions, ask for consent and make an appointment to obtain written consent. This appointment can take place at the patient’s home and the important other is also invited to attend. After written consent from both parties is obtained, the first questionnaires are completed (T0) and the electronic monitoring device is explained and handed out. Since evidence suggests that adherence will be statistically higher when patients start to use the electronic monitoring device [38], a run-in period of 35 days (+/− 7 days) is incorporated. A second appointment is made to coincide with the end of the run-in period (T1), during which a second set of questionnaires is completed by patient and important other, and EM data is collected. Group assignment is revealed after questionnaires have been completed. For the following 6 months patients allocated to the experimental group receive the intervention and the control group receives CAU. Six months after T1 participants are asked to complete questionnaires and EM data is collected (T2). Subsequently, patients continue using the EM device for the follow-up period of 6 months and questionnaires are also completed at the end of this 6 months (T3) (see Fig. 1 for flow-diagram) .

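### The interim is triggered by inclusions, not by completed T2 outcomes, so if the trigger is applied as written the look carries less than the half information that the 0.029 level appears to assume

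*Protocol article*

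**What the plan says.** Protocol article, Power calculation: "we will perform an interim analysis when half of the participants have been included". The same section gives the planning rates ("The intervention group showed an adherence proportion of 95.1% and the control group a proportion of 79.1" per cent), the error rates ("We applied a 2-sided alpha of 0.029 and a power of 0.80") and the size ("Anticipating a drop-out of 10%, this led to a target of 81 participants in both groups, a total of 162"). It names no stopping boundary and no separate level for the interim.

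Protocol article, Primary outcome measure: "The proportion of days adherent over the 35–215 day period (T1-T2) will be calculated". Primary study parameter: the quantity tested is "the proportion of participants that is adherent more than 95% of the 180 days (T1-T2) in both randomization groups", by a chi-square test with continuity correction.

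Under Randomization and Procedure, patients are allocated 1:1 only after a run-in of 35 days (plus or minus 7). T2 is six months after T1.

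Procedure also reports: "Inclusion commenced in September 2018, but inclusion is recently stopped due to Covid-19. Data collection is still ongoing". It does not give the number included, whether the stop is permanent, or whether the interim has taken place.

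**The concern.** The trigger counts an event at the start of a patient's participation, while the outcome to be compared exists only some seven months later. When the 81st patient is included, that patient has not yet been randomised, and nobody included in the preceding 215 days has a complete primary outcome.

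Two things are at stake. First, the trial is sized and tested at 0.029 rather than 0.05, presumably because of this look. If the look has little chance of detecting the planned effect, that price buys little. Second, a level of 0.029 suggests two equal looks with the first at half information, and the trigger does not deliver that. The reported stop of inclusion adds a practical question: if enrolment is over, stopping early for efficacy saves no recruitment.

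**Working it through.** **Inputs.** Rates 0.951 and 0.791, two-sided alpha 0.029, power 0.80, dropout 10%, 81 per group (Power calculation); outcome complete at day 215 (Primary outcome measure); chi-square with continuity correction (Primary study parameter). Accrual time is not stated, so it is an assumption with a range.

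**1. The plan's own size.** The arcsine formula reproduces it. h = 2·arcsin√0.951 − 2·arcsin√0.791 = 0.503. n = 2·((2.183 + 0.842)/0.503)² = 72.3, so 73 per arm. 73 × 1.10 = 80.3, so 81 per arm and 162 in total. The evaluable target is therefore 2 × 73 = 146, and half of it is 73 patients, or 36 to 37 per arm.

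**2. What 0.029 appears to assume.** Take two looks at the same two-sided nominal level, bivariate normal with correlation √t, where t is the information fraction at the first look. At t = 0.5, two looks at 0.029 give an overall level of 0.0494; the level giving exactly 0.0500 is 0.0294. So 0.029 fits an equal-level design with the look at half information. This is an inference, because no boundary is named.

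**3. Information at the trigger.** With uniform accrual of 162 over A months and a lag of 215 days (7.06 months), the number with T2 data when 81 are included is (162/A)·(A/2 − 7.06) = 81 − 162·7.06/A, before dropout. The second term is positive for any A, so the count is always below 81.

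**4. Interim power.** Exact binomial enumeration of the continuity-corrected test at 0.029 and the planning rates:

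| Accrual of 162 (assumed) | With T2 data | t | Per arm | Power, planned test |
|---|---|---|---|---|
| 18 months | 81 − 63.6 = 17 | 0.11 | about 8 | 0.1% |
| 24 months | 81 − 47.7 = 33 | 0.21 | about 16 | 5% |
| 36 months | 81 − 31.8 = 49 | 0.30 | about 24 | 11% |
| Half of evaluable target | 73 | 0.50 | 36 | 27.5% |

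At the extremes, 12 months of accrual gives no patient with T2 data and 60 months gives 62 (t = 0.38). If included is read as randomised, the lag is 180 days and the counts become 28, 41 and 54 (t = 0.17, 0.25, 0.34): a smaller gap, but still short of half.

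**5. Type I error.** Normal theory with both looks at 0.029 gives 0.056, 0.054 and 0.053 at t = 0.11, 0.21 and 0.30. The ceiling, for independent looks, is 1 − 0.971² = 0.0572. The planned test is conservative. Simulating two looks with the continuity correction (interim at 8, 16, 24 or 36 per arm, final at 73 per arm) gives an overall error of 0.018 to 0.027 at a common rate of 0.79, 0.013 to 0.019 at 0.87, about 0.006 at 0.95, and at most about 0.030 at 0.50 to 0.65.

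**6. Value of dropping the look.** At 73 per arm with the planned test, final power is 0.69 at 0.029 and 0.80 at 0.05. Without the continuity correction the figures are 0.80 and 0.86.

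**The case against.** The best defence is that the sentence may mean that the first half of the participants is analysed once their outcome is available, with the data cut and boundary set out in the full protocol or analysis plan. That is possible, and absent mechanics are not held against a journal article. But the trigger itself is stated here, and on its face it is inclusion. If the charitable reading is what was intended, one added phrase settles it.

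Three stronger readings are tempting and are not supported:

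- A reader might infer that two looks at 0.029 push the overall error above 5%. That holds only under normal theory, and then by less than one percentage point. With the test the article specifies, the overall error stays at or below about 0.03.
- A reader might infer that the look would be nearly empty. That needs all 162 to be enrolled in about 18 months or less. At 24 to 60 months, 41% to 76% of the first 81 would have T2 data. The article gives no accrual rate.
- A reader might infer that the Covid-19 stop has already invalidated the size and power. The number included and the permanence of the stop are not stated. If enrolment ended short of 162 but above 81, the look's share of the final information rises, and 0.029 at both looks can become conservative (normal theory: 0.0473 at t = 0.6). If fewer than 81 were included, the trigger is never met and 0.029 is simply a strict final level.

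It is also fair to say that the trial was sized at 0.029, so the planned power already allows for that level.

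**Conclusion.** The concern holds in a limited form. As worded, the interim trigger is tied to the wrong event. If 162 are enrolled, the look falls short of half information at any accrual speed. Under assumed uniform accrual over 18 to 36 months, its power for the planned effect is about 0.1% to 11% with the specified test, against 27.5% at half of the evaluable target. The harm is an interim that can tell little, not a loss of type I error control.

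The sizes rest on the assumed accrual times, on uniform entry, on the planning rates of 95.1% and 79.1%, and on counts taken before dropout. That 0.029 belongs to an equal-level two-look design is inferred. What follows from the stop of inclusion is conditional on facts that the article does not give. This is an inexpensive improvement to a stated rule, not a flaw that threatens the trial's validity.

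**What to change.** Reword the trigger so that the interim takes place when T2 electronic monitoring data are complete for half of the evaluable target, about 73 patients. This is a one-line amendment to be made before any unblinded look. Its cost is a later interim, by which time more of the 162 will have been enrolled and the look can save less recruitment.

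If the stop of inclusion is permanent and no interim comparison has been made, record before any unblinding that the interim is dropped and that the final test is at two-sided 0.05. In either case, if fewer than 162 are randomised, restate the power or the detectable difference for the number actually randomised, using the continuity-corrected test that is planned. If an interim comparison has already been made, the level cannot simply be returned to 0.05; the look and the number of T2-complete patients it used should be reported.
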